### Participants and selection criteria

Participants of this study will include MLPs who manage HIV-positive children attending the CTCs in Tanga and pairs of HIV-positive children and their caregivers.

#### Midlevel providers (MLPs)

We will invite a minimum of two MLPs from each CTC of the intervention arm to take part in the nutrition training. We will also recruit a similar number of MLPs from the CTCs of the control arm. A total of 32 MLPs will participate in this study. MLPs include assistant medical officers, clinical officers, allied health workers, and nurse assistants. We will exclude all other health workers that do not fulfill the MLP criteria as per its definition. Such health workers include health promotion volunteers and non-clinician, home-based care staff.

#### HIV-positive children

We will recruit HIV-positive children attending the selected CTCs. Inclusion criteria for participation of the HIV-positive children are: aged 6 months to 14 years; registered or transferred to the CTCs; attended with his/her caregiver; consent by the caregiver to voluntarily participate in the study. We will exclude children whose ART information is missing in the medical records and whose HIV sero-status has not been confirmed. An estimated 800 children currently attend the 16 selected CTCs. Because half of the CTCs will be selected for the intervention arm, approximately half of the potential participants (400) will be in the intervention group and a similar number for the control group.

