**Methods/Design:**

We will conduct a cluster randomized controlled trial in care and treatment centers (CTCs) in Tanga, Tanzania. The CTCs will be the unit of randomization. We will select 16 CTCs out of 32 for this study, of which we will randomly assign 8 to the intervention arm and 8 to the control arm by coin flipping. From the selected CTCs we will attempt to recruit a total of 800 HIV-positive children aged 6 months to 14 years, half of whom will be receiving care and/or treatment in the CTCs of the intervention arm, and the other half of whom will be receiving care and/or treatment in the CTCs of the control arm (400 children in each condition).

We will provide nutrition training to MLPs of the CTCs selected for the intervention arm. In this intervention, we will use the World Health Organization guidelines on nutrition training of health workers for HIV-positive children aged 6 months to 14 years. The trained MLPs will then provide tailored nutrition counseling to caregivers of children being treated at the 8 CTCs of the intervention arm. We will measure nutrition status and child feeding practices monthly for a total of six months.

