#### Sample size estimation

To calculate the minimum sample size for the intervention and control group, we assumed the inter-cluster coefficient to be as low as 0.01. Also, we assumed that 8 clusters (CTCs) would be included in the intervention arm and a similar number in the control arm. We could not find any other studies, based in sub-Saharan Africa, that estimated weight gain after implementing this type of intervention, and therefore we used a similar study conducted in China investigating children in the general population as a reference [21]. In this study, an estimated mean weight gain difference between children of the intervention and control arm was 0.3 kg in six months. To detect the mean difference of 0.3 kg weight gained in the intervention group compared to the control group over a 6-month duration, at a power of 80% and 5% significant level, 24 participants per cluster will be needed. In total, a minimum sample size of 192 participants for each arm will be required to produce the desired effect. To counteract the effect of loss to follow-up, deaths, a number of outcome variables, and missing data, we will attempt to recruit 400 HIV-positive children for the intervention arm and a similar number for the control arm. Therefore, an estimated 800 caregivers will also be recruited to participate in this study, with a similar distribution between the intervention and control groups (400 in each arm).

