### Randomization process

We will use the CTCs as the unit of randomization. A total of 32 CTCs provide care and treatment to about 1,800 HIV-positive children aged 0 to 14 years old in Tanga. We will exclude private CTCs, as well as CTCs with less than 20 HIV-positive children. A total of 16 CTCs in the area are public and have at least 20 HIV-positive children receiving care and/or treatment; they also represent all the districts of the region. Of the 16 CTCs, 4 are from the Tanga urban area; this is due to a high number of CTCs and HIV-positive patients attending them. All CTCs based in district hospitals will be selected in this study because they fulfill the selection criteria. These 16 CTCs will be eligible for the randomization process: a coin toss to assign 8 CTCs to the intervention arm and 8 to the control arm. A person who is not a member of the study research team will conduct the randomization process.

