### Data collection

Prior to data collection, we will train research assistants on the data collection and ethical procedures. We will translate the English questionnaire into Swahili and then back-translate it to English using two independent local researchers to check that is retains its original meaning. We will use the Swahili version of the questionnaire for data collection. The trained research assistants will conduct a pre-test for the questionnaire and the interview in the Swahili language. We will collect data from August 2013 and continue to do so monthly for a period of six months. To assess changes in the MLPs knowledge, we will use the questionnaire from the training manual to collect data before and after the nutrition training.

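### The article presents allocation of CTCs before recruitment and sets no registration cut-off, so it does not exclude enrolling children after the allocation is known

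*Protocol article*

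**What the plan says.** The eligibility criteria (Participants and selection criteria, HIV-positive children) admit children who are "registered or transferred to the CTCs", who attend with a caregiver and whose caregiver consents. No date is given by which a child must be on the register.

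Allocation is by CTC (Randomization process): "a coin toss to assign 8 CTCs to the intervention arm and 8 to the control arm". On who does it, the same section says: "A person who is not a member of the study research team will conduct the randomization process". It does not say when the result is disclosed or who recruits the children.

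Wherever an order can be read, allocation comes first. The abstract (Methods/Design) assigns the CTCs and then continues: "From the selected CTCs we will attempt to recruit a total of 800 HIV-positive children aged 6 months to 14 years". Study design describes the toss, and the Baseline subsection that follows it assesses children who are already recruited. Sample size estimation sets targets by arm: "we will attempt to recruit 400 HIV-positive children for the intervention arm and a similar number for the control arm".

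The HIV-positive children section also gives the size of the pool: "An estimated 800 children currently attend the 16 selected CTCs". The timing of measurement is in Data collection: "We will collect data from August 2013 and continue to do so monthly for a period of six months".

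**The concern.** Randomising clinics makes the arms comparable for children who are identified independently of the allocation. It gives no such protection to children who are approached, or whose caregivers decide, once the arm is known. Here the arm cannot be hidden for long. Two MLPs per intervention CTC are trained and then counsel caregivers, so staff know their arm and caregivers can learn it.

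Entry depends on attending and on consent. Both may change when a clinic is known to offer nutrition counselling. If caregivers in one arm are more motivated, or their children sicker, the arms differ for reasons the toss did not create. The direction cannot be foretold: such a difference could imitate a training effect or hide one. Recruiting more children does not shrink it. Data analysis provides for adjustment for confounders, but that reaches only what is measured, and the Measurements and HIV CTC related data sections list no variable for motivation or care-seeking.

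**Working it through.** **Order of events.** No sentence places listing, consent or baseline before or after the toss. The abstract and Study design present assignment first, the sample size section recruits for named arms, and the eligibility rule has no closing date. A team that followed the text in the order given could toss, disclose and then recruit without departing from it.

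**The plan's own figure.** From Sample size estimation: 8 clusters per arm, 24 children per cluster, intracluster coefficient 0.01, difference 0.3 kg, power 80%, level 5%. Then 8 × 24 = 192 per arm, as stated. The 24 itself cannot be reproduced because no SD is given, so I solved for the SD:

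- Design effect: 1 + (24 − 1) × 0.01 = 1.23.
- Effective number per arm: 192 / 1.23 = 156.1.
- Implied SD (two-sided, normal): 0.3 × √(156.1 / 2) / (1.960 + 0.842) = 0.95 kg.
- Other conventions give 1.07 kg (one-sided) or 0.88 kg (two-sided, one cluster per arm deducted).

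**Size of a possible bias.** Let a net share f of one arm be recruited differentially, and let those children's expected six-month weight gain differ by d from the rest. The arm mean moves by f × d. If the share arises from uptake u₁ in one arm and u₀ in the other, f = (u₁ − u₀) / u₁. For example, uptake of 100% against 80% gives f = 0.20. Values of f and d are assumptions, as the article gives neither.

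- Low: f = 5%, d = 0.25 kg: bias 0.05 × 0.25 = 0.0125 kg, or 0.0125 / 0.3 = 4% of the target difference.
- Middle: f = 10%, d = 0.5 kg: bias 0.05 kg, or 17%.
- High: f = 20%, d = 1.0 kg: bias 0.20 kg, or 67%.

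**Effect on the false-positive rate.** The standard error is SD × √(2 × design effect / n per arm), with the SD at 0.946 kg before rounding.

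- At 192 per arm: 0.946 × √(2 × 1.23 / 192) = 0.107 kg.
- At 400 per arm (50 per cluster, design effect 1 + 49 × 0.01 = 1.49): 0.946 × √(2 × 1.49 / 400) = 0.082 kg.

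The two-sided rejection rate with no true effect, nominally 5%, becomes:

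| Case | Bias | 192 per arm | 400 per arm |
|---|---|---|---|
| Low | 0.0125 kg | 5.2% | 5.3% |
| Middle | 0.05 kg | 7.5% | 9.4% |
| High | 0.20 kg | 46% | 69% |

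The rate is higher with 400 per arm because the standard error falls and the bias does not.

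**A single scenario for comparison.** Uptake of 80% against 60% gives f = 0.20 / 0.80 = 25%. With d of 0.25 to 0.5 SD at 0.95 kg, the bias is 0.25 × 0.95 × 0.25 = 0.06 kg to 0.5 × 0.95 × 0.25 = 0.12 kg, or 20% to 40% of the target. It lies inside the wider range and rests on equally unsupported inputs, so the wider range is the fairer statement.

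**The case against.** The strongest reply is that the article never says children are recruited after the allocation is known. The order of sentences is an order of presentation. The even split in the HIV-positive children section, "approximately half of the potential participants (400) will be in the intervention group", is a forecast rather than a procedure. An article may also leave enrolment dates to the full protocol. This stands, and it limits the point to what the text fails to exclude. It does not remove the point, because the order that the text does present, with targets by arm and an undated eligibility rule, is the unprotected one.

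A reader might go further and infer that children brought to a CTC after its staff are trained will be enrolled. The documents do not support that. Baseline is described before the intervention and is measured on recruited children. The six monthly assessments fall in one window from August 2013, which a late entrant could not complete. A reader might also take the transfer wording to mean transfers after the toss. It may mean only children who moved in earlier and are already on the rolls. The idea that staff would keep ART records differently by arm, and so alter who is excluded, has no basis in the text either.

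The near-census is a real mitigant: with 800 sought from about 800 attending, there is little room to choose among children. It is not complete protection. The 800 attending is an estimate made before refusals and before the exclusions for missing ART information or unconfirmed serostatus. The stated minimum of 192 is only 192 / 400 = 48% of the target per arm, so uptake could differ between arms while the sample size is still met. The outside person who tosses the coin protects how the allocation is made, but not who learns it before consent.

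**Conclusion.** The point holds in a limited form. The article does not exclude identifying and consenting children after the allocation is known to CTC staff and caregivers. It does not show that this will happen. The baseline stage, the fixed window and the near-census point to enrolment near the start among existing patients. What remains is differential consent or attendance by arm, which adjustment for measured confounders would correct only in part.

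The size depends on inputs that are not in the article: roughly 4% to 67% of the 0.3 kg target for f of 5% to 20% and d of 0.25 to 1.0 kg. The bias in kilograms does not depend on the SD. The false-positive rates do, and they rest on the back-solved 0.95 kg and the plan's coefficient of 0.01. Weight gain is the scale of the sample size calculation, whereas Data analysis names underweight, wasting, stunting and feeding practices as outcomes, so the figures are an illustration and not a prediction for those outcomes. The change is worth making because it is cheap and removes the doubt by design.

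**What to change.** State and follow this order:

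1. On one date, fix the list of eligible children in all 16 CTC registers, including those already transferred in, and apply the record-based exclusions as of that date.
2. Complete consent and the baseline assessment in all 16 CTCs.
3. Only then hold the toss, or disclose its result if it has been held, and start the training.
4. Limit the primary analysis set to children registered by the fixed date, analysed in their CTC of enrolment even if they later move. This agrees with the stated intention-to-treat principle. Report later arrivals separately, if at all.

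The cost is a delay of about one monthly visit cycle before the toss and training, since patients attend monthly (Study area). Sample size, staff and measurements are unchanged. Trial status says the trial is still being formulated, so the order can be set now. If this order is already intended, a dated sentence in Randomization process and a cut-off date in the eligibility criteria would settle the matter.

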#### Caregivers of the HIV-positive children

We will recruit caregivers of HIV-positive children for this study because our study involves children aged 6 months to 14 years, who cannot give consent themselves to participate in the study nor can they participate in the study alone. Furthermore, the nutrition counseling conducted by the MLPs will target the children’s caregivers. We will therefore be recruiting a similar number of caregivers as there will be children. As in previous studies [3,20], we will use the definition of a caregiver as a child’s parent, relative, guardian, or anyone else above 18 years old who takes care of the child, supervises their treatment, and accompanies the child to the CTC.

#### Sample size estimation

To calculate the minimum sample size for the intervention and control group, we assumed the inter-cluster coefficient to be as low as 0.01. Also, we assumed that 8 clusters (CTCs) would be included in the intervention arm and a similar number in the control arm. We could not find any other studies, based in sub-Saharan Africa, that estimated weight gain after implementing this type of intervention, and therefore we used a similar study conducted in China investigating children in the general population as a reference [21]. In this study, an estimated mean weight gain difference between children of the intervention and control arm was 0.3 kg in six months. To detect the mean difference of 0.3 kg weight gained in the intervention group compared to the control group over a 6-month duration, at a power of 80% and 5% significant level, 24 participants per cluster will be needed. In total, a minimum sample size of 192 participants for each arm will be required to produce the desired effect. To counteract the effect of loss to follow-up, deaths, a number of outcome variables, and missing data, we will attempt to recruit 400 HIV-positive children for the intervention arm and a similar number for the control arm. Therefore, an estimated 800 caregivers will also be recruited to participate in this study, with a similar distribution between the intervention and control groups (400 in each arm).

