### Measurements

#### Nutrition status

We chose the nutrition status of HIV-positive children as the outcome variable, including use of the categories underweight, wasting, and stunting. We will measure children’s weight using a standardized hanging Salter® scale (UK) calibrated to 0.1 kg for children who cannot stand and a standardized Seka® digital scale (Brooklyn, USA) for children who can stand. Height will be measured for children aged 24 months and older using a Seka® measuring rod calibrated to 0.5 cm [22]. We will use a designated mark on a board to measure lengths of children younger than 24 months in a recumbent position [23].

After obtaining height and weight data, we will convert them to a height-for-age z-score, weight-for-age z-score, and weight-for-height z-score [24] using the Epi-Info ENA Ver. 3.5.1, 2008 (CDC, Atlanta, Georgia, USA) software and WHO reference values [25,26]. Low height-for-age, weight-for-height, and weight-for-age are measures of stunting, wasting, and underweight, respectively [27].

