### Data analysis

We will analyze the data based on the intention-to-treat principle. We will use both descriptive and regression analyses. For the descriptive analyses, we will conduct both χ^2^ and Student’s *t*-tests to examine the differences in characteristics of participants in the intervention and control groups. This study will have two types of outcome variables. First, nutrition status measured as underweight, wasting, and stunting. Second, feeding practices measured by feeding frequency, dietary diversity, and the quality and quantity of foods consumed. We will use multiple logistic regression analyses to examine the effectiveness of nutrition training on nutrition status and feeding practices of the two arms while adjusting for confounding variables. We will also conduct analyses to see monthly changes in feeding practices and nutrition status and to compare the intervention and control arms. To examine the independent association of nutrition counseling by trained MLPs on outcome variables, we will use repeated measures of ANOVA and Generalized Estimated Equation.

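### The trial is sized on mean weight gain in kg, which is neither a listed outcome nor analysed, and the 80% power is not shown for any outcome that is

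*Protocol article*

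**What the plan says.** Under Sample size estimation, the effect comes from a study of general-population children in China, in which "an estimated mean weight gain difference between children of the intervention and control arm was 0.3 kg in six months". On clustering, "we assumed the inter-cluster coefficient to be as low as 0.01" and "we assumed that 8 clusters (CTCs) would be included in the intervention arm and a similar number in the control arm". The purpose of the calculation is stated as: "To detect the mean difference of 0.3 kg weight gained in the intervention group compared to the control group over a 6-month duration". The result is that "at a power of 80% and 5% significant level, 24 participants per cluster will be needed", so that "a minimum sample size of 192 participants for each arm will be required to produce the desired effect". The target is then raised to 400 per arm to cover losses, deaths, missing data and the number of outcomes, without a calculation.

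Under Measurements, Nutrition status: "We chose the nutrition status of HIV-positive children as the outcome variable, including use of the categories underweight, wasting, and stunting". Weight and height are measured in order to derive height-for-age, weight-for-age and weight-for-height z-scores.

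Under Data analysis, two types of outcome are listed: "First, nutrition status measured as underweight, wasting, and stunting"; and then feeding practices (frequency, dietary diversity, quality and quantity of food). Effectiveness is examined by multiple logistic regression with adjustment for confounders. Monthly changes are also compared between arms, and repeated-measures ANOVA and GEE are applied to the outcome variables.

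**The concern.** A power statement is informative only for the variable, effect and test it was calculated for. Here it was calculated for a difference in mean kilograms gained. The plan then defines its outcomes without that variable and uses, as its main test, a model that needs a binary response. No control rate, target difference or power is given for any binary outcome, and no SD or effect for any z-score.

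This is more than detail left to an analysis plan: the article itself states the sizing variable, the outcome list and the model, and they do not match. What is at stake is interpretation. A null logistic result for underweight or wasting could be read as evidence that training does not work, on the strength of an 80% figure that was never worked out for those outcomes.

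**Working it through.** **Inputs**
- From Sample size estimation: difference 0.3 kg; 80% power; 5% significance (two-sided assumed, as sidedness is not stated); ICC 0.01; 8 clusters per arm; 24 children per cluster; target 400 per arm (50 per cluster).
- From Study area: among regional under-fives, about 12% underweight, 5.5% wasted and more than 49% stunted. These are proxies only. The same section says that nutrition data on HIV-positive children in the region are not available.

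**The plan's own figure.** 8 × 24 = 192 is right. The design effect is 1 + (m − 1) × ICC:
- m = 24: 1 + 23 × 0.01 = 1.23; effective n per arm = 192 / 1.23 = 156.1
- m = 50: 1 + 49 × 0.01 = 1.49; effective n per arm = 400 / 1.49 = 268.5

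No SD of weight gain is stated, so the 24 per cluster cannot be reproduced forward. Solving for the SD gives 0.3 / (1.960 + 0.842) × √(156.1 / 2) = 0.95 kg. Other conventions (one-sided; no design effect; t with 14 df; one fewer cluster) give 0.88 to 1.07 kg. So 192 is plausible for mean weight gain, but not verifiable.

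**What 80% power needs for the listed categories.** With control prevalence p and intervention prevalence q, solve

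(p − q) / √{[p(1 − p) + q(1 − q)] / n_eff} = 1.960 + 0.842 = 2.80

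| Outcome | Control | Needed at 192 per arm | Needed at 400 per arm, no attrition |
|---|---|---|---|
| Underweight | 12% | 3.6% (70% relative fall) | 5.3% (56%) |
| Wasting | 5.5% | 0.3% (95%) | 1.2% (79%) |
| Stunting | 49% | 33.6% (32%) | 37.1% (24%) |

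Check for underweight at 192: √[(0.12 × 0.88 + 0.036 × 0.964) / 156.1] = 0.0300, and 0.084 / 0.0300 = 2.80. A pooled-variance version of the formula changes these prevalences by about 0.1 percentage point.

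**Power if a prevalence were halved.** Power = Φ{(p − q) / SE − 1.960}.
- Underweight, 12% to 6%: variance sum 0.1056 + 0.0564 = 0.162. SE is 0.0322 at 192 and 0.0246 at 400, giving power of about 46% and 69%.
- Wasting, 5.5% to 2.75%: variance sum 0.0520 + 0.0267 = 0.0787. SE is 0.0225 and 0.0171, giving about 23% and 36%.

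So even a halving of underweight or wasting falls short of 80% at the full target with nobody lost.

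**The case against.** Several points on the other side have force.

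- **The plan claims no power for the binary outcomes.** This stands. A reader might infer that the stated 80% is false for them. The documents do not support that: no binary effect is specified, so there is no claim to refute. What can be said is that the 80% does not carry over.
- **The categories are not the only analysed outcomes.** This also stands. Feeding practices are listed, z-scores are derived, and repeated-measures ANOVA and GEE are planned, so a continuous z-score analysis is compatible with the text. These methods are applied to the listed outcome variables, though, which do not include kilograms gained, and no sample size is given for a z-score analysis.
- **The target is 400, partly because there are several outcomes.** This is fair, and the 400 column is the kinder test. But the same increase must also absorb losses, deaths and missing data.
- **The regional rates may be too low.** The Background reports underweight 4.6 times and wasting 9.6 times as likely in ART-treated HIV-positive children, and the trial enrols to age 14. With an assumed 40% underweight, 80% power needs a relative fall of about 37% at 192 per arm and 29% at 400. The conclusion on underweight and wasting is therefore conditional on the proxies.
- **Covariates and monthly measures could add precision.** They could. The single-comparison figures do not include that gain.

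A reader might also go further, assume a between-child weight SD of 1.5 to 6 kg, and conclude that a 0.3 kg effect gives only about 5% to 27% power for underweight at 12%. That SD is not in the documents, and much of the shortfall comes from using attained weight without baseline information, not from cutting it into categories. It is not relied on here.

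**Conclusion.** The mismatch stands on the text alone: the sizing variable is absent from both the outcome list and the analysis, and 80% power is not shown for any listed outcome, feeding practices included. At the regional rates, 80% is unlikely for underweight and wasting, which would need relative falls of 56% and 79% even at 400 per arm. Stunting is nearer, at about 24%, but only with full retention.

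These sizes rest on two-sided 5%, equal cluster sizes, the ICC of 0.01 carried over to the binary outcomes, regional under-five rates as proxies, and one unadjusted end-of-study comparison. They show what the design could detect. They do not show that the trial would miss a true effect.

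**What to change.** Name six-month weight gain in kg, adjusted for baseline weight, age and sex, as the primary outcome. Analyse it with a linear model that accounts for clustering by CTC, and state the SD behind the 24 per cluster. Keep underweight, wasting and stunting as secondary outcomes.

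Alternatively, make change in weight-for-age z-score the primary outcome and restate the power on that scale, with its SD, target effect and ICC.

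Either route changes wording only; weight and height are already collected monthly. The small cost is that the headline becomes a mean difference, though prevalences can still be reported. Whether the feeding outcomes are also analysed as continuous is a matter of preference and not part of this point.
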